#### Handling missing data

Missing values in clinical and psychometric variables (BAI, BDI-II, MIDAS, HIT-6, MSQ total score), as well as missing body mass index (BMI) values, were handled using multiple imputation by chained equations (MICE) implemented in R (2), based on Fully Conditional Specification, whereby each incomplete variable was imputed using a separate regression model appropriate to its distribution. Regarding neuroimaging data, missing or incomplete MRI datasets were not imputed. Across centres, minor differences in acquisition resulted in variable numbers of volumes, particularly in resting-state fMRI sequences. To ensure comparability across sites, resting-state datasets were temporally harmonised by retaining an equivalent number of volumes for all subjects included in the analyses.

In addition, datasets affected by excessive head motion, defined as motion artefacts that could not be adequately corrected using standard motion-correction algorithms during preprocessing, were excluded from neuroimaging analyses. This quality-control step was applied uniformly across centres to minimise motion-related bias and to preserve the validity of functional connectivity and perfusion measures.

No imputation was performed for missing neuroimaging data; analyses were conducted on quality-controlled datasets only.

#### Data quality assessment

Each participating centre was responsible for the collection, entry and local storage of clinical and biological data, and for implementing site-specific monitoring procedures in accordance with national regulations for open-label phase IV studies. Cross-centre checks of data quality and internal consistency were periodically performed, and any discrepancies were resolved through review of source documents and discussion between investigators until consensus was reached (39).

#### Descriptive and inferential statistics

All computations were conducted via *R* software (version 4.4.0). Quantitative variables were compared using the cross-sectional Mann–Whitney test, whereas categorical variables were assessed via the chi-square test or Fisher’s exact test. A value of *p* < 0.05 was considered statistically significant. The statistical plan included baseline comparisons between R and NR across clinical, anamnestic, psychological, and disability measures. Variables were also compared between healthy controls and migraine patients, stratified for gender and diagnosis. Predictive thresholds for circulating serum *α*-CGRP, IL-1β, and TNF-α levels were estimated in patients using binomial logistic regression (generalised linear model, GLM).

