### Sample size calculation

In the absence of a reliable biomarker for predicting the response to antimigraine drugs, we considered, on an empirical basis supported by the limited available data, the difference in baseline methylation levels of CpG islands of the RAMP1 gene, a key receptor subunit of calcitonin gene-related peptide (CGRP), between migraine subjects who are responders and those who are non-responders to CGRP-targeting mABs.

The minimum sample size was inferred considering previous exploratory epigenome-wide association scans (EWAS) in migraine. Wan D. et al. (16) found that the methylation level of CpG islands of the RAMP1 gene, a key receptor subunit of CGRP, was significantly lower in females living with migraine than in healthy female volunteers (2.18% ± 1.91% vs. 5.85% ± 5.41%). Taking this variance into account, we computed a sample size of 47 participants per group (80% power, 5% significance level). Moreover, we considered a 6% loss of participants. Given the rate of >75% response to erenumab observed in randomised clinical trials (30%), as well as the rate of <25% response, we required a minimum sample size of 168 subjects with migraine at baseline and 51 controls.

This sample-size calculation was designed to support the proof-of-concept biomarker-discovery component of the study and was not intended to provide statistical power for definitive high-dimensional machine-learning model development. Therefore, machine-learning analyses are considered exploratory and hypothesis-generating, with the aim of reducing dimensionality and prioritising candidate multimodal predictors for future validation in larger independent cohorts.

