### Interventions

#### Subjects living with HFEM or CM

They are assessed at baseline, then they receive a 3-month course of treatment with erenumab, a mAb targeting the CGRP receptor. The choice to use erenumab was dictated by the fact that it was the first and, at the time the trial began, the only CGRP-targeting mAb available on the European market.

No concomitant migraine preventive treatment was allowed during the screening, baseline and the 3-month treatment period. Abortive medications were allowed, but the type and formulation had to be the same throughout the study. Their usage was registered as well.

Their responders/non-responder status was defined assessed at the end of the 3-month treatment cycle, based on the headache diary data. Patients were classified as responders (R) if they achieved a ≥50% reduction in monthly headache days (MHD) during the final 4 weeks of the 12-week erenumab treatment period compared with the 4-week baseline run-in period. Patients who achieve a <50% reduction in MHD were classified as non-responders (NR). Within the R group, super responders (SR) were defined as patients who achieve a ≥ 75% reduction in MHD over the same period. Within the NR group, full non-responders (FNR) were defined as patients who achieve a < 25% reduction in MHD over the same period.

At visit 1, inclusion/exclusion criteria were reviewed; demographics and clinical characteristics were recorded. To avoid sample heterogeneity and to identify and minimise confounding factors, all participants underwent a structured interview to collect demographic information, including age, sex, ethnicity; clinical information including habits of caffeine, tobacco and drug consumption, physical activity level; life-time comorbidities, medication use, menstrual status and migraine-related information.

At this visit, participants started recording their headache characteristics in an *ad hoc* diary for a month to confirm the diagnosis at the following visit.

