### Statistical analysis

#### Efficacy endpoint analyses

The primary objective of the study is to identify a panel of biomarkers that is reliably associated with response to treatment in a substantial proportion of patients with migraine. To this end, we will develop classification algorithms that assign patients to response categories defined on an ordinal scale. Supervised machine-learning approaches based on parametric, semi-parametric and non-parametric models are going to be fitted and compared. The optimal model will be selected according to predefined performance criteria, including area under the curve (AUC), accuracy, precision and recall.

Secondary analyses will characterise differences between migraine patients and healthy controls at baseline in: (i) DNA methylation profiles; (ii) structural and functional magnetic resonance imaging measures; and (iii) pharmacogenetic, biochemical, clinical and psychological variables. Within the migraine cohort, we will also compare DNA methylation, brain morphometry and functional connectivity, as well as pharmacogenetic, biochemical, clinical and psychological measures, among patients classified as responders and non-responders to CGRP-targeting mABs.

Given the prospective design, changes in clinical status, disability and psychometric measures, from baseline to the end of the treatment period, are going to be evaluated to quantify the impact of the therapy and to relate these changes to treatment response categories. In parallel, longitudinal differences in structural and functional magnetic resonance imaging measures among response groups are going to be examined to identify treatment-related brain changes and estimate their effect sizes in relation to drug exposure and clinical improvement (e.g., reduction in monthly headache days).

Finally, plasma concentrations of CGRP, IL-1β and TNF-*α*, together with their messenger RNA expression in peripheral blood mononuclear cells, are going to be assessed over the course of treatment to explore treatment-related alterations in peripheral inflammation and their correlation with clinical endpoints, including headache frequency, acute medication intake and disability.

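### Baseline measures are related to treatment response only through response categories, although the diary supplies each patient's percentage reduction in headache days; a full-scale analysis should stand beside responder v non-responder.

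*Protocol article*

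**What the plan says.** Under Interventions, response is the change in monthly headache days from the 4-week run-in to the last 4 weeks of a 12-week treatment period. Responders (R) reach a reduction of at least 50%, and "Patients who achieve a <50% reduction in MHD were classified as non-responders (NR"). Super-responders (SR, at least 75%) and full non-responders (FNR, below 25%) are subsets. All four labels are cut from one percentage.

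Baseline data meet response in these places:

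- **Efficacy endpoint analyses.** Methylation, brain morphometry and connectivity, and genetic, biochemical, clinical and psychological measures are compared "among patients classified as responders and non-responders to CGRP-targeting mABs".
- **Descriptive and inferential statistics.** "The statistical plan included baseline comparisons between R and NR across clinical, anamnestic, psychological, and disability measures". The general method is that "Quantitative variables were compared using the cross-sectional Mann–Whitney test", with chi-square or Fisher's exact test for categorical variables. CGRP and cytokine thresholds come from binomial logistic regression.
- **Preprocessing and feature selection.** Each candidate predictor is screened against response category by t-test or ANOVA, or by chi-square. Those showing no association are dropped.
- **Primary objective and Handling of class imbalance.** The classifiers target ordered response categories, with four classes given as an example.

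The continuous scale appears only for on-treatment data: Efficacy endpoint analyses relates MRI change to the reduction in monthly headache days, and CGRP and cytokine changes to headache frequency, among other endpoints.

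**The concern.** In an R v NR comparison, a patient with a 49% reduction counts as the opposite of one with 51% and as the same as one who got worse. The size of the reduction is discarded although the diary already records it. The first objective is to find differences linked to response in a modest discovery sample, so lost information raises the chance of missing a real biomarker and lets patients near 50% drive the result. In the predictor screen a miss carries forward, because the variable does not enter the models.

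The article gives no reason for leaving the full scale out of the baseline analyses. Its limitations section defends the 12-week time point, not the categorisation.

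**Working it through.** **1. The plan's own figure.** Sample size calculation says "we computed a sample size of 47 participants per group (80% power, 5% significance level"), citing methylation "significantly lower in females living with migraine than in healthy female volunteers (2.18% ± 1.91% vs. 5.85% ± 5.41"%).

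- Difference: 5.85 − 2.18 = 3.67.
- Pooled SD: √[(1.91² + 5.41²)/2] = 4.06, so d = 3.67/4.06 = 0.905. This needs 20 per group (two-sided 5%, 80% power).
- Larger SD: d = 3.67/5.41 = 0.678. This needs 35 per group.

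Neither gives 47. Working backwards, 47 per group detects d = (1.96 + 0.84)√(2/47) = 0.578, or 0.584 with the t correction. The next step does follow: 47/0.94 = 50 and 50/0.30 = 167, against the stated 168. Because "we considered a 6% loss of participants", the evaluable number is 168 × 0.94 ≈ 158. There are therefore three candidate effects, and I carry all of them.

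**2. Assumptions.** Biomarker and reduction are bivariate normal. SR and FNR are each 30% (Sample size calculation; the FNR share is read as equal to the SR share). The responder share at 50% is not given; I use 40–60%. Each d is read as SR v FNR, the groups that drive the total of 168.

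**3. From d to a correlation.** For 30% tails the cut-point is c = 0.524, the tail mean is m = φ(c)/0.30 = 1.159, and the tail variance is v = 1 + cm − m² = 0.265. Then d = 2ρm/√(1 − ρ² + ρ²v). Solving gives ρ = 0.246 for d = 0.584, ρ = 0.284 for d = 0.678 and ρ = 0.370 for d = 0.905.

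**4. Power by formula (n = 157).** Full scale: Φ(arctanh(ρ)√(n − 3) − 1.96). Cut: two-sample t-test at the R v NR difference that ρ implies, for example d = 0.401 when ρ = 0.246 and the split is even.

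| Effect (SR v FNR) | Full scale | Cut, 50:50 | Loss, 50:50 | Loss at 40% or 60% |
|---|---|---|---|---|
| 0.584 | 87.7% | 70.4% | 17.3 | 18.4 |
| 0.678 | 95.2% | 82.5% | 12.7 | 13.6 |
| 0.905 | 99.8% | 97.1% | 2.7 | 3.1 |

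At a responder share of 30%, or by symmetry 70%, the loss at d = 0.584 is 21.9 points. If d = 0.584 is read as the R v NR difference itself, power is 99.5% v 95.3%, a loss of 4.2 points.

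**5. Simulation with rank tests (n = 158, responder share 40–60%).** At d = 0.584, Spearman correlation with the continuous reduction has about 85% power and Mann–Whitney on R v NR 67–69%, a loss of about 16–18 points. At d = 0.678 the loss is about 13 points, and at d = 0.905 about 3–4. With whole-day diary counts on baselines of 8–25 days, d = 0.584 gives 84% v 67%. Null rejection rates were 4.3–5.2%.

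**6. Do the finer categories rescue it? (d = 0.584)**

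| Analysis | Power |
|---|---|
| Spearman, continuous reduction | 85% |
| Trend across four ordered classes | 80% |
| SR v FNR, Mann–Whitney | 78% |
| R v NR, Mann–Whitney | 67–69% |
| Four-class ANOVA (order ignored) | 67% |

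The ANOVA named for the screen recovers none of the loss; a test that respects the order recovers most of it.

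**7. Other shapes.** If the biomarker steps exactly at 50%, the cut wins (94% v 86%). If only super-responders differ, the full scale wins (73% v 55%); likewise if only full non-responders differ (71% v 55%).

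**The case against.** Four points deserve a hearing.

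- **The plan is not confined to the 50% cut.** A reader might infer that it is. The primary models target ordered categories, four classes are illustrated, and the sample size rests on the extreme groups. This stands: the accurate statement is that response enters only as categories. The named screening tests nonetheless ignore the order.
- **An unadjusted Mann–Whitney test is not shown to be the test for every biomarker.** The list in "The statistical plan included baseline comparisons between R and NR across clinical, anamnestic, psychological, and disability measures" covers clinical rather than molecular or imaging measures. The biomarker contrast under Efficacy endpoint analyses names no test. Mitigation of confounding factors and Acquisition protocol mention covariates and site. This stands too. It affects the exact power figures, not the fact that response is categorised.
- **R v NR is the question asked.** The first objective and the Aim are both worded as responders against non-responders. This argues against replacing the contrast or reducing it to description, but not against adding to it.
- **The article is condensed and a full analysis plan is not shown.** A supportive analysis could sit there. But the article names the contrasts and tests and uses the continuous scale elsewhere, so as written it fixes the choice for baseline data.

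**Conclusion.** The point holds in limited form. No stated analysis relates a baseline measure to the continuous reduction in headache days. The power cost of the 50% cut is about 16–18 points at d = 0.58, about 13 at d = 0.68 and about 3–4 at d = 0.905. These figures rest on a linear-normal relation, about 158 evaluable patients, 30% tails, an assumed responder share of 40–60%, and each d being read as SR v FNR.

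A reader might take the largest of these as the loss at the plan's own effect size. The documents do not support that. The value 0.58 is back-solved from 47 per group, and the published means and SDs do not reproduce it. Those figures also compare women with migraine and healthy women, whereas the contrast of interest is "between migraine subjects who are responders and those who are non-responders to CGRP-targeting mABs". The plan therefore has no observed effect for response groups, and only the range can be defended.

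This is a worthwhile, inexpensive improvement to a discovery analysis. It does not invalidate the R v NR comparison.

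**What to change.** Keep R v NR as the stated contrast. Under Efficacy endpoint analyses and Descriptive and inferential statistics, add one prespecified full-scale analysis for each baseline biomarker. Either of these would do:

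- Spearman correlation with the percentage change in monthly headache days; or
- regression of headache days in the final 4 weeks on the biomarker, with run-in headache days and the plan's existing covariates.

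Choose one before the response-group results are seen, and report both analyses for every biomarker.

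The cost is plan wording and one further analysis per biomarker, with no new data. Status of the study says the stratified analysis is in progress, so the addition should be dated and labelled as made at that stage. The drawbacks are a second result per biomarker that is less direct to read clinically, and lower power than R v NR if a biomarker truly switches at 50%.

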#### Mitigation of confounding factors

Given the real-world observational design of the BIOMIGA study, several measures were adopted to minimise the influence of potential confounding factors. Clinical outcome classification were based on prospectively collected headache diaries, which represent the reference standard for the assessment of migraine outcomes in real-world studies and reduce recall bias through systematic longitudinal recording of headache frequency and acute medication use (39). Standardised eligibility criteria limited major sources of confounding, including medication overuse headache, concomitant preventive treatments, severe neurological or psychiatric disorders, cardiovascular diseases, substance abuse, and other medical conditions potentially affecting biomarker levels or treatment response.

Demographic and clinical variables, including age, sex, migraine subtype, disease duration, baseline monthly migraine days, disability measures, acute medication intake, and relevant comorbidities, were systematically collected and evaluated as potential confounders. Analyses aimed at identifying clinically meaningful cut-offs for circulating CGRP concentrations were performed using GLM for prespecified clinical and demographic covariates to estimate independent associations while accounting for potential confounding. For epigenetic analyses, standardised procedures were adopted to minimise pre-analytical variability. Quality-control procedures and batch-effect correction methods were applied where appropriate, and known determinants of DNA methylation variability, including age, sex, medication exposure, and lifestyle-related factors such as smoking habits, were considered during statistical analyses to reduce potential confounding.

To reduce variability in neuroimaging-derived measures, MRI data were acquired using standardised acquisition protocols and processed through harmonised quality-control and preprocessing pipelines. Structural and functional MRI datasets underwent visual and automated quality assessment, with exclusion of scans affected by major artefacts or excessive motion.

Established preprocessing procedures, including motion correction, spatial normalisation, and nuisance signal regression for functional MRI data, were applied to minimise non-biological sources of variability. In addition, demographic and imaging-related factors known to influence brain measures, such as age, sex, and head motion parameters, are going to be considered during statistical modelling and feature selection procedures.

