
#### Model evaluation and validation

These models are going to be evaluated within a nested cross-validation framework, with inner loops for hyperparameter tuning and outer loops for performance estimation, to ensure an unbiased assessment of generalisation performance. All transformations, feature-selection procedures, class-balancing strategies and hyperparameter optimisation steps are going to be confined to the training folds and then applied to the corresponding validation/test folds. For RF models, predictive performance will also be assessed using the out-of-bag (OOB) error rate, which provides an internal estimate of generalisation performance without the need for a separate validation set. OOB misclassification rates and class-specific OOB errors are going to be examined as global and category-specific performance indicators. For models evaluated using cross-validation, performance is going to be quantified using a combination of metrics, including balanced accuracy, sensitivity, specificity, positive and negative predictive values and area under the receiver operating characteristic curve (AUC), allowing comparison across algorithms in the presence of class imbalance.

This multi-step modelling strategy was designed to balance predictive performance, robustness and interpretability in the context of a complex, high-dimensional biomarker dataset. Because the final model specification depends on the observed data structure and on the retained feature set, the complete algorithmic configuration, selected hyperparameters and final validation results are going to be reported in the subsequent results manuscript. A schematic overview of the machine-learning pipeline, including preprocessing, feature selection, model training, validation and performance evaluation, is provided in Figure 3. This workflow illustrates the sequential and nested structure of the analysis and highlights the measures adopted to minimise overfitting and information leakage.

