Specific challenges concern the measurement of circulating CGRP. CGRP has been proposed as the most promising candidate biomarker in migraine, but studies measuring its concentrations in peripheral blood and other biofluids have yielded conflicting results, owing to differences in sampling timing, assay sensitivity and specificity, and the episodic nature of peptide release (15). Recent work has started to clarify pre-analytical stability, suggesting that plasma levels are robust under controlled conditions (49), yet there is still no consensus on clinically meaningful thresholds or on the optimal sampling paradigm. BIOMIGA mitigates some of these issues through rigorous standard operating procedures and central laboratory analyses, but limited time-point measurements may not fully capture individual calcitonin gene-related peptide dynamics and could under-estimate within-person variability. Secondarily, despite evaluating patients in a pain-free state, patients living with CM determine the difficulty in having fully pain-free days within the allowed window of access, therefore possibly determining a higher variability of CGRP level or functional connectivity at the MRI scan between the ictal and interictal phases.

Other limitations are inherent to the complexity of the biomarker programme and to the application of ML approaches to high-dimensional, multimodal data. The large number of clinical, neuroimaging and molecular variables relative to the sample size increases the risk of overfitting and of identifying spurious associations, even when structured feature-selection strategies, class-imbalance handling and internal validation procedures are applied. Although BIOMIGA adopts advanced ML methodologies, including penalisation techniques and cross-validation frameworks, the resulting predictive models should therefore be regarded as exploratory and hypothesis-generating.

In addition, the absence of an independent external validation cohort limits the immediate generalisability of the proposed models. Performance estimates derived from internal validation approaches, such as out-of-bag estimation and cross-validation, may remain optimistic in the context of complex, multicentric datasets. Replication in larger, independent cohorts will be essential to confirm the robustness, stability and clinical relevance of the identified biomarker signatures.

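### The logistic-regression cut-offs for α-CGRP, IL-1β and TNF-α are called predictive or clinically meaningful, but no internal validation is stated for them

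*Protocol article*

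**What the plan says.** Two sections of the protocol article describe the analysis.

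- *Descriptive and inferential statistics* sets out "Predictive thresholds for circulating serum" α-CGRP, IL-1β and TNF-α, and says that these "levels were estimated in patients using binomial logistic regression (generalised linear model, GLM"). The same section takes p<0.05 as significant.
- *Mitigation of confounding factors* returns to CGRP alone: "Analyses aimed at identifying clinically meaningful cut-offs for circulating CGRP concentrations were performed using GLM for prespecified clinical and demographic covariates". The variables listed there as potential confounders are "age, sex, migraine subtype, disease duration, baseline monthly migraine days, disability measures, acute medication intake, and relevant comorbidities".

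Neither section names the outcome category, the rule that turns a fitted model into a cut-off, or any data split, resampling or optimism correction.

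Validation is described in *Model evaluation and validation*: "These models are going to be evaluated within a nested cross-validation framework". That sentence follows the list of random forest, support vector machine, neural network, nearest-neighbour, tree and boosting models. *Sample size calculation* and *Preprocessing and feature selection* call the machine-learning analyses exploratory. *Limitations and future directions* accepts that for CGRP "there is still no consensus on clinically meaningful thresholds".

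**The concern.** A single blood-marker threshold is the result of this study that could most easily be carried into practice. It carries the strongest labels in the article, while the stated safeguards against over-optimism belong to a different set of analyses. Biochemical variables do enter the cross-validated random forest models, but that does not validate a separate threshold from a logistic model.

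Two things are at stake. If the threshold is picked because it separates responders well in these patients, its apparent accuracy in the same patients is too favourable, and a marker with no association can look useful. Second, the step from the adjusted model to one cut-off is not fixed, so it could be settled after the data are seen.

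**Working it through.** **Is there a figure in the plan to reproduce?** No. The article gives no accuracy or error rate for the cut-offs, so the size has to come from stated assumptions.

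**Inputs**
- Patients: 168 less 6% loss (*Sample size calculation*): 168 × 0.94 = 157.9, taken as 158.
- Responders: 30–50%, assumed. The article names no outcome for the thresholds.
- Significance level: 0.05 (*Descriptive and inferential statistics*).
- Marker: normally distributed, equal variance in both groups (assumed).
- Cut-off: the value with the largest Youden index J = sensitivity + specificity − 1 (assumed; the article states no criterion). The dichotomised marker is then tested by chi-square in the same patients.

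**Step 1. Does the adjusted model give one cut-off?** Write logit(p) = a + b·m + g′z, with m the marker and z the covariates. The marker value at a chosen probability p₀ is

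m* = [logit(p₀) − a − g′z] / b.

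Unless g = 0, m* changes with age, sex, migraine subtype and the other covariates. A common cut-off needs one more rule, for example a fixed dichotomy entered in the model, or averaging over the covariate distribution.

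**Step 2. Optimism if the cut is chosen from the data** (simulation, 158 patients, 30–50% responders)

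| Marker | Direction of effect | Apparent J | True J at the chosen cut | p<0.05 |
|---|---|---|---|---|
| No association | either | 0.13–0.15 | 0 | about 40% |
| No association | fixed in advance | 0.09–0.10 | 0 | about 23% |
| AUC 0.60 | either | 0.21–0.22 | 0.12–0.13 | not applicable |

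Balanced accuracy is 0.5 + J/2, so the first row corresponds to about 0.57 where the truth is 0.50.

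**Step 3. Three markers, assumed independent.** At least one false threshold with p<0.05:
- searched in either direction: 1 − (1 − 0.40)³ = 0.78;
- direction fixed: 1 − (1 − 0.23)³ = 0.54;
- no search, one prespecified test each: 1 − 0.95³ = 0.143.

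**Step 4. Optimism from fitting the covariates.** Here the cut is placed on the score from a logistic model fitted to pure noise (158 or 168 patients, 30% or 50% responders). With the marker alone, apparent AUC is 0.53–0.54 and apparent balanced accuracy 0.56–0.57. With nine noise covariates added (nine is an assumption; the article lists about eight types), they are 0.64–0.65 and 0.63–0.64. In new subjects all are 0.50. The AUC involves no cut-off search, so that part comes from fitting alone.

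**Step 5. Precision under a fixed rule.** Take a marker with AUC 0.60 and the cut set where the predicted probability is 0.5. The 95% range of the estimated cut-off was about −1.7 to +1.9 SD at 50% responders. At 30% it was about +1.0 to +12.9 SD, much of it outside the data. The tails are heavy, so these limits are approximate.

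**The case against.** The strongest case against the point is that it reads much into silence. A journal article may leave the cut-off criterion and its validation to the full protocol or analysis plan, which are not shown. Saying that thresholds were estimated in patients may only distinguish patients from controls. Several stronger readings therefore go beyond the text:

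- A reader might infer that the whole sample was used and no validation was done. The article says neither; what can be said is that none is stated.
- A reader might infer that the thresholds will be over-optimistic, with false-positive rates near 40% per marker or 80% over three. The article states neither a search for the cut-off nor a test of the dichotomised marker. With one prespecified test per marker the rates are 5% and 14.3%.
- A reader might infer that an adjusted model cannot yield a common threshold. It can, given a further rule as in Step 1.
- A reader might apply the clinically meaningful label to all three markers. It is used for CGRP only, and as an aim; the predictive label covers all three.

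The general framing also helps. *Study design* speaks of candidate profiles and exploratory multivariable approaches, the study is called proof-of-concept, and *Limitations and future directions* says that later studies must confirm the output. The statement there about lack of consensus on CGRP thresholds is a fair caveat, not an error.

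These objections limit the wording but do not remove the point. The article does state a method and a strong label for the thresholds, and it describes validation at length for the machine-learning models only. A fixed cut-off rule would remove the search, but not the optimism from fitting covariates or the need for an interval (Steps 4 and 5).

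**Conclusion.** The concern holds in a conditional form. As written, the plan produces thresholds labelled predictive (three markers) and clinically meaningful (CGRP), with no internal validation stated for them and no rule for moving from the adjusted model to one cut-off. If the cut-off is chosen from the data, apparent sensitivity and specificity are too high and the naive p-value too small. Under the best-Youden assumption the gain in J that is not real is about 0.13–0.15 for a null marker (0.09–0.10 with the direction fixed), and roughly 0.09 for a marker with AUC 0.60.

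These sizes rest on 158 patients, 30–50% responders, normal markers and a data-driven cut. They show what the stated method leaves open; they are not consequences that the article itself fixes.

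**What to change.** - Analyse α-CGRP, IL-1β and TNF-α as continuous terms in the adjusted logistic model, and name the response category used as outcome.
- If a cut-off is reported, state the rule that produces it. Derive it inside the nested cross-validation already planned, or in a bootstrap that repeats the whole selection.
- Report optimism-corrected sensitivity and specificity, and a confidence interval for the cut-off.
- Give no unadjusted p-value for a marker dichotomised at a cut-off chosen from the same data.
- Label these thresholds exploratory, as is already done for the machine-learning results, in place of predictive and clinically meaningful.

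The cost is one resampling loop and a few sentences, and the reported accuracy will look less favourable. No new data are needed. *Status of the study* says that processing for the stratified groups is still under way, so the change can be made before the results are reported.
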